# An Internet-Based Intervention (Condom-Him) to Increase Condom Use Among HIV-Positive Men Who Have Sex With Men: Protocol for a Randomized Controlled Trial

**DOI:** 10.2196/resprot.2723

**Published:** 2013-10-13

**Keywords:** HIV-positive, men having sex with men, condom use, self-efficacy, intention, HIV prevention, pilot study, intervention

## Abstract

**Background:**

In the recent years, the Internet has been used as a medium to find sexual partners and engage in risky sexual behavior. This has changed the way in which men having have sex with men (MSM) seek sexual partners and has increased the number of high-risk sexual encounters. Therefore, developers of human immunodeficiency virus (HIV)-prevention interventions have also started using the Internet as a viable medium to promote safe sexual behaviors. However, much of the efforts thus far have been aimed at HIV-negative rather than HIV-positive MSM. HIV-positive individuals continue to engage in risky sexual behaviors and thus constitute an important group in which HIV prevention strategies need to be addressed. Therefore, HIV prevention in HIV-positive MSM is a critical issue.

**Objective:**

Condom-Him, an Internet-based intervention tailored to increase condom use among HIV-positive MSM, was developed with the aim of improving condom use, self-efficacy, and intentions to use condoms among these individuals. The acceptability and feasibility of this Internet-based intervention will be examined in a pilot study.

**Methods:**

We will perform a randomized controlled parallel-group superiority trial. HIV-positive MSM who currently engage in unprotected anal sex will be recruited for the study. Participants will be randomly assigned using a one-to-one allocation ratio generated by the computer program. The researchers will be blinded to participant’s group assignment. Participants will be assigned either to use the Condom-Him intervention (experimental arm) or to view a list of websites containing HIV/AIDS related information (control arm). Self-administered questionnaires will be provided online before randomization (baseline) and two weeks after intervention (post-test).

**Results:**

The study will include a total of 60 participants with 30 in each group. The results from this pilot study will provide further evidence for a larger study to examine the effectiveness of this intervention and will provide a cost-effective and widely accessible approach to HIV prevention for HIV-positive MSM.

**Conclusions:**

Internet-based interventions for HIV-positive MSM, a population that has been under-represented in the efforts for positive prevention of HIV within Canada, have the potential to provide a cost-effective strategy, which influences the way in which information is accessed and provided to high-risk individuals. The advantages of an Internet-based intervention include the potential to provide consistency in the delivery of an intervention and the ability to disseminate the intervention to a wider population. Internet-based interventions are perceived as vital tools in combating HIV infection within the realm of social media. Therefore, it is important to determine the feasibility and acceptability of these interventions before implementing them.

**Trial Registration:**

Clinicaltrials.gov: NCT01726153; http://clinicaltrials.gov/ct2/show/NCT01726153 (Archived by WebCite at http://www.webcitation.org/6Jljzip8B).

## Introduction

### Overview

The number of human immunodeficiency virus (HIV)-positive individuals continues to increase in Canada. Among the high-risk groups, the group of men having sex with men (MSM) accounted for the greatest proportion (44%) of new infections in 2008 [1]. Various studies, which target the sexual risk behaviors of HIV-positive MSM, have found that 10% to 60% of these individuals do not routinely practice safe sex [2]. In addition, MSM recently infected with HIV had a median of 20 sexual partners within the previous year, and they continued to repeatedly engage in high-risk sexual behavior, particularly unprotected anal intercourse [3]. Moreover, 34% of MSM recently diagnosed with an HIV infection did not change their risk behaviors after the diagnosis of their condition, and 20% actually increased their risk behaviors after the diagnosis [3]. The potential outcomes of engaging in unprotected sex with partners who are HIV-negative or whose status is unknown are the possibility of infecting others with HIV and putting oneself at risk for contracting sexually transmitted infections (eg, syphilis, gonorrhea, and herpes virus infection) [4]. Many individuals who engage in risky sexual behaviors use the Internet to meet their sexual partners, and the Internet itself may facilitate such risk-taking behaviors [5,6]. In keeping with the current trends, the individuals working in the field of prevention of HIV infection need to incorporate the same medium as that used by high-risk individuals to reduce risky sexual behaviors. Thus, developing technological innovations such as Internet-based interventions is critical.

### Computer-Based Online Interventions

Computer-technology-based interventions (CBIs) [7] provide an alternative to human-delivered interventions for prevention of HIV infection. Noar, Black, and Pierce [8] defined CBIs as those that use computer technology as the primary or sole medium for intervention delivery. To date, few trials of health interventions that use computer technology and are conducted entirely online have been performed [9]. In the case of such interventions, all aspects of the study must be implemented online, that is, participant recruitment, randomization process, data collection, and delivery of the actual intervention. Many of the current CBIs recruit participants using methods other than the Internet and collect data in a face-to-face format, and only provide the actual intervention online.

### Advantages of Internet-Based Studies

Previously, HIV prevention interventions were mainly delivered on individual or group levels. However, many clinical and community settings do not have adequate human resources required for implementation of such methods [8]. Therefore, the ability to disseminate efficacious interventions into many practice settings remains limited. In addition, the barriers and challenges of intervention fidelity have limited the public health impact of behavioral HIV prevention interventions [8]. CBIs have the advantage of providing consistency in the delivery of an intervention and enable participants to initialize their participation in the study at any time of the day and at a location convenient to them. Online participation removes barriers such as scheduling times and human resources that may restrict participants’ participation or the ability to provide the intervention to a number of individuals. For example, individuals in rural settings, for whom it may be difficult to access the resources, would able to participate in the CBIs without the costs associated with travel and/or taking time off from work. Further, the anonymity provided by Internet-based interventions is an advantage, specifically to those who may feel stigmatized. For instance, individuals who have not yet disclosed their HIV infection status and who may feel hesitant about participating in an intervention geared towards those who are HIV-positive could participate in such CBIs because the disclosure factor would not be relevant with an Internet-based intervention. In addition, a previous study has shown that typically, participants answering questionnaires online report higher rates of sexual behavior than in pen-and-paper or interview formats [7]. Moreover, the cost associated with Internet-based interventions is low, and human facilitators are not required for implementation of the intervention; therefore, the intervention can be run on numerous occasions. In addition, the data collection methods are less costly because questionnaires do not have to be mailed to the participants, and in-person are not required for collecting data [9]. Finally, online data collection is quicker, because the need for booking appointments or mailing questionnaires is eliminated. Online questionnaires are immediately available to participants for completion, and thus provide immediate accessibility to the data.

### Interventions to Foster Condom Use Among HIV-Positive MSM

Previously, HIV prevention programs were primarily focused on HIV-negative subjects or subjects whose HIV status was unknown. Safe sex behaviors such as condom use should also be practiced by HIV-positive individuals. However, little attention has been focused on interventions targeting this population. The National Institute of Health and the Centers for Disease Control and Prevention have identified a need for behavioral interventions in HIV-positive individuals [10]. To fill this scientific gap, we plan to conduct an online pilot randomized controlled trial (RCT) to evaluate the acceptability and feasibility of Condom-Him, an Internet-based intervention developed to promote condom use among HIV-positive MSM with partners who are HIV-negative or whose status is unknown.

The primary outcome of the tailored Internet-based intervention is to increase condom use among HIV-positive MSM. The primary objective of this study is to examine the overall acceptability and feasibility of the tailored Internet-based intervention. The secondary objective of this study is to examine the preliminary efficacy of the tailored Internet-based intervention in increasing self-efficacy and intention to use condoms.

## Methods

### Study Design

The design of the proposed pilot study to evaluate the acceptability and feasibility and acceptability of the tailored Internet-based intervention in increasing condom use among HIV-positive MSM is a randomized controlled parallel-group superiority trial (NCT01726153). The flow of participants within the randomized control trial is shown in Figure 1. Participants will be randomly assigned using a one-to-one allocation ratio. Random assignment will occur only after participants have completed baseline questionnaires. The random assignment will be performed by the computer system that has been programmed by the computer/Web-intervention programmer. Participants cannot be blinded to their assigned arm. Individuals within the control arm receiving a list of various websites will be aware they have not been allocated to use the tailored Internet-based intervention. Participants in the experimental arm (Condom-Him) will be aware that they have been allocated to use the tailored Internet-based intervention. The researcher will be blinded to the participant’s treatment assignment. The research assistant, who will be downloading the data, will be the only individual aware of the participant’s assignment. The research assistant will not have any participation in the random assignment of participants because this process does not involve any individuals and is entirely performed using the computer program. The outcomes of the study will be collected at two time points: pre-intervention (T0) and two weeks after intervention (T1). The participants will be sent an email two weeks after the intervention to remind them to revisit the study website to complete the post-test questionnaires. The study has been approved by the research ethics board of both the academic and research institutions.

### Experimental Arm: Condom-Him

The tailored Internet-based intervention Condom-Him was designed to increase condom use, self-efficacy in condom use, and intention to use condoms among HIV-positive MSM and their partners who are HIV-negative or whose HIV infection status is unknown. The welcome page of the Condom-Him intervention study is shown in Figure 2. Condom-Him is a tailored interactive single session lasting approximately one hour. The single session is tailored to the specific needs of the participants determined from their responses to the baseline questionnaire about self-efficacy and intention to use condoms. The intervention was tailored on the basis of cutoff scores for self-efficacy and intention measures. On the basis of their responses, the participants are classified into the high or low self-efficacy in condom use groups. A cutoff score of 0-23 indicates high self-efficacy, and a cutoff score of 24-48 indicates low self-efficacy. In addition, the intention to use condoms was also tailored using a cutoff score of 0-2, which indicated a low intention, and a score of 3, which indicated a high intention to use condoms. Subsequently, the participants were profiled into one of the four possible profiles: (1) high self-efficacy and intention, (2) low self-efficacy and intention, (3) low self-efficacy and high intention, and (4) high self-efficacy and low intention. The participants were then guided through the online session by a virtual “peer”, who provides tailored intervention messages particular to their profile in addition to providing stories and videos and interactive activities to increase self-efficacy and intention to use condoms. The single session is divided into three segments to increase condom use, self-efficacy in condom use, and intention to use condoms as follows: (1) planning condom use when having anal intercourse, (2) negotiating the use of a condom with a partner, and (3) choosing not to have sexual intercourse without a condom.

Within each of the three segments of the intervention, participants are given tailored messages pertaining to the focus of the segment. The Intervention Mapping method was used to develop the intervention. This process consists of six consecutive steps to systematically develop health promotion programs using theory, empirical evidence from the literature, and additional evidence from research [11]. The theory-informed methods and practical strategies selected to increase condom use practices of the target population were consistent with the social cognitive theory and the theory of planned behavior.

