### Planned Inclusion Criteria

Individuals will be selected to participate in the study if they meet the following preset inclusion criteria: (1) 18 years of age or older, (2) HIV-positive, (3) MSM, (4) engage in unprotected anal intercourse with a partner who is HIV-negative or whose HIV infection status is unknown, (5) read English, and (6) have access to a computer and the Internet.

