### Intention to Use Condoms

To measure the intention of the participants to use condoms, participants are asked three questions about their intentions over the next 6 months to use a condom. The scale is a 2-point response (“certainly not”/“yes certainly”). The psychometric properties of the measure show good internal consistency; Cronbach alpha=.89 [13].

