#### Analysis to Address Study Objectives

Independent *t* tests will be used to examine the differences between the control and experimental groups in terms of the participants’ self-efficacy, intention to use condoms, and actual condom use before the intervention and 2 weeks after the intervention.

Descriptive statistics will be used to examine the acceptability rating of the intervention. In addition, qualitative responses of the participants to open-ended questions about what they find most and least appealing about the Condom-Him will be analyzed to identify the strengths and weaknesses of the intervention as perceived by the participants. Recruitment and retention rates for the control and experimental groups will be used to determine the feasibility of the intervention and online data collection methods. Lastly, descriptive statistics will be used to examine the utilization of the intervention.

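### The planned post-test t test for intention is valid but ignores the baseline intention score, whose top value is also the plan's high-intention category; adjusting for it would give a more precise estimate at no cost

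*Protocol article*

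**What the plan says.** All references are to the protocol article.

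- **Intention to Use Condoms:** "participants are asked three questions about their intentions over the next 6 months to use a condom", and "The scale is a 2-point response".
- **Experimental Arm: Condom-Him:** the session is "tailored using a cutoff score of 0-2, which indicated a low intention", and "a score of 3, which indicated a high intention to use condoms". Crossing this with high or low self-efficacy gives four profiles, of which the first and third are high intention.
- **Interventions to Foster Condom Use Among HIV-Positive MSM:** the secondary objective is "preliminary efficacy of the tailored Internet-based intervention in increasing self-efficacy and intention to use condoms".
- **Study Design:** the baseline questionnaires are completed before random assignment.
- **Analysis to Address Study Objectives:** independent t tests compare the two arms on self-efficacy, "intention to use condoms, and actual condom use before the intervention and 2 weeks after the intervention". No change score, baseline adjustment or breakdown by profile is stated.
- **Planned Inclusion Criteria:** the behavioural requirement is that participants "engage in unprotected anal intercourse with a partner who is HIV-negative or whose HIV infection status is unknown". No criterion concerns intention.

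**The concern.** The plan expects some participants to enter with the highest possible intention score, because two of its four profiles are written for them. These participants can only stay at 3 or fall. The objective is worded as an increase, and the stated test takes the post-test mean of each arm without regard to where anyone started.

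The cost is precision. Participants who start at 3 and mostly stay there differ from the rest mainly because of their starting point. An unadjusted test treats that spread as noise, although the trial has already recorded what explains it. The Results section says that the pilot will enable the design of a larger trial, so a needlessly imprecise intention estimate would carry into that design.

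**Working it through.** **1. Score range.** Three items scored 0/1 give a minimum of 3 × 0 = 0 and a maximum of 3 × 1 = 3. The coding is inferred, but it fits the published cut-offs. Scoring 1/2 would give 3 to 6 and leave the 0-2 category empty. From a baseline of 3 the possible gain is 3 − 3 = 0, in either arm.

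**2. The plan's own figure.** The only sample-size basis is 10 cases per independent variable. A total of 60 needs 60 / 10 = 6 variables. Their number is not stated, so 60 can be neither reproduced nor refuted. The article gives no effect size, standard deviation or power for intention, and this point does not depend on the 60.

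**3. What the ceiling does to the average.** Let c be the share starting at 3 in both arms. If only gains matter, the whole-arm difference is (1 − c) times the effect in those scoring 0-2. With an assumed standardised effect of 0.8 and c = 50%, this is 0.5 × 0.8 = 0.40. At 30 per arm and two-sided 5%, t-test power falls from 0.87 (no ceiling) to 0.34. This describes the average effect in the people enrolled; it is not a bias.

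**4. What baseline adjustment recovers.** This was simulated with 30 per arm and two-sided 5%. All of the following are assumptions, none from the article:
- a share c starts at 3, and the rest at 0/1/2 with probabilities 0.5/0.25/0.25;
- of those starting at 0-2, 20% (control) or 60% (experimental) reach 3, and the others move little within 0-2;
- 90% of those starting at 3 stay there in both arms.

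| Share at 3 at baseline | Planned t test | Whole sample, adjusted for baseline | Gain (points) |
|---|---|---|---|
| 10% | 0.72 | 0.80 | 8 |
| 20% | 0.61 | 0.75 | 14 |
| 30% | 0.53 | 0.68 | 15 |
| 50% | 0.35 | 0.52 | 17 |
| 60% | 0.27 | 0.43 | 16 |

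With no one at 3, the t test has about 80% power and adjustment adds about 5 points. Repeat runs, which differ in random seed and in how non-reachers move, put single gains between 8 and 17 points. About 10-16 is a fair summary for shares of 10-60%. With no true effect, both analyses reject in about 5-6% of trials.

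**5. A smaller effect.** With 20% v 40% reaching 3 and half at the ceiling, power is 0.12 for the t test and 0.17 adjusted. Over the ceiling shares tried, the gain is about 4-8 points.

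**6. If the session also protects high intention.** Let half start at 3, with 60% (control) v 95% (experimental) of them staying there, and 20% v 40% of the rest reaching 3. Power is 0.29 for the planned t test, 0.44 adjusted in the whole sample, and 0.15 for a Fisher test restricted to those starting at 0-2. The adjusted whole-sample analysis gains here too, while the restricted one does worse than the plan.

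**The case against.** The strongest reply is that nothing in the plan is wrong. The t test is a valid randomised comparison of the average effect in everyone eligible, and if some enter at the top of the scale the average effect really is smaller. This stands.

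A reader might go further and infer that the ceiling makes the planned comparison misleading, and that the analysis should be confined to participants scoring 0-2. The article does not support that, for three reasons:
- The objective is stated for the intervention as a whole and names no low-intention subgroup.
- The share at the ceiling is not given. Recruiting men who currently have unprotected anal intercourse may keep it small.
- High-intention profiles also receive tailored messages, so an effect on keeping intention high is plausible, and a restricted analysis would miss it (step 6).

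A reader might also infer that two profiles cannot benefit at all. That holds for the intention score only: the third profile has low self-efficacy, and both can improve condom use.

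Two further objections stand in part. First, this is a pilot whose primary objective is acceptability and feasibility, so the consequence is limited. Second, covariate adjustment is often left to an analysis plan, which is not at hand. The article does name a specific test, however, and the comment is about that stated test. The gain from adjustment also does not need a ceiling, as it is about 5 points without one.

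**Conclusion.** The point holds as one of efficiency, not of validity. Given 0/1 coding, high intention is the top of the scale, and the stated test makes no use of a baseline score that the trial collects before randomisation and already uses for tailoring. Adjusted analysis had higher power in every scenario with a true effect, without inflating the error rate materially.

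The size depends on assumptions that the article cannot confirm: the ceiling share and the 20% v 60% effect, which is large for a one-hour session. At the smaller effect, neither analysis has useful power at 30 per arm, and the benefit is mainly a narrower confidence interval. This is a modest but worthwhile correction to a secondary analysis.

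**What to change.** In Analysis to Address Study Objectives, replace the post-test t test for intention with a between-arm comparison at T1 in the whole sample, adjusted for baseline intention. Report the adjusted difference with its confidence interval.

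As descriptive support only, report by arm:
- the proportion reaching 3 at T1 among those with a baseline of 0-2;
- the proportion still at 3 among those with a baseline of 3.

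Give the numbers in each group, so that the ceiling share is known when the larger trial is planned. The 0-2 comparison should not replace the whole-sample analysis. It rests on fewer people (about 30 of 60 if half start at 3) and cannot show an effect on maintaining intention.

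The cost is a change of wording. No new data, instrument or recruitment is needed.

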**Figure 1 figure1:**
[figure not shown]
Flow of participants through randomized control trial. As the study is in progress, some n='s are left blank.

